# A randomised controlled trial of the clinical effectiveness, safety and cost-effectiveness of adalimumab in combination with methotrexate for the treatment of juvenile idiopathic arthritis associated uveitis (SYCAMORE Trial)

**DOI:** 10.1186/1745-6215-15-14

**Published:** 2014-01-09

**Keywords:** Adalimumab, Juvenile idiopathic arthritis, Methotrexate, Ophthalmology, Paediatric, Rheumatology, Safety, Uveitis

## Abstract

**Background:**

Juvenile idiopathic arthritis (JIA) is the most common rheumatic disease in children. Children with JIA are at risk of inflammation of the uvea in the eye (uveitis). Overall, 20% to 25% of paediatric uveitis is associated with JIA. Major risk factors for development of uveitis in JIA are oligoarticular pattern of arthritis, an age at onset of arthritis of less than seven years of age, and antinuclear antibody positivity. In the initial stages of mild to moderate inflammation the uveitis is asymptomatic. This has led to current practice of screening all children with JIA for uveitis. Approximately 12% to 38% of patients with JIA develop uveitis in seven years following onset of arthritis. In 30% to 50% of children with JIA-associated uveitis structural complications are present at diagnosis. Furthermore about 50% to 75% of those with severe uveitis will eventually develop visual impairment secondary to ocular complications such as cataract and glaucoma. Defining the severity of inflammation and structural complications in uveitis patients is now possible following Standardised Uveitis Nomenclature (SUN) guidelines, and modified to incorporate the consensus of end point and outcome criteria into the design of randomised trials. Despite current screening and therapeutic options (pre-biologics) 10% to 15% of children with JIA-associated uveitis may develop bilateral visual impairment and certified legally blind. To date, there remains no controlled trial evidence of benefits of biologic therapy.

**Methods/design:**

This study will randomise 154 patients aged 2 to 18 years with active JIA-associated uveitis (despite methotrexate (MTX) treatment for at least 12 weeks). All participants will be treated for 18 months, with follow up of 3 years from randomisation (continuing on MTX throughout). All participants will receive a stable dose of MTX and in addition either adalimumab (20 mg/0.8 ml for patients <30 kg or 40 mg/0.8 ml for patients weighing 30 kg or more, subcutaneous (s/c) injection every 2 weeks based on body weight), or placebo (0.8 ml as appropriate according to body weight) s/c injection every 2 weeks.

**Discussion:**

This is the first randomised controlled trial that will assess the clinical effectiveness, safety and cost effectiveness of adalimumab in combination with methotrexate for the treatment of juvenile idiopathic arthritis associated uveitis.

**Trial registration:**

ISRCTN10065623

## Background

Juvenile idiopathic arthritis (JIA) is the most common rheumatic disease in children. Children with JIA also are at risk of inflammation of the uvea in the eye (uveitis). Overall, 20% to 25% of all paediatric uveitis is associated with JIA [1,2], but a greater proportion is seen in referral cohorts. The major risk factors for the development of uveitis in JIA patients are oligoarticular pattern of arthritis, age at onset of arthritis younger than 7 years and antinuclear antibody positivity [3]. In the initial stages of mild to moderate inflammation, uveitis is entirely asymptomatic. This has led to the current practice of screening all children with JIA regularly for uveitis. Approximately 12% to 38% of patients with JIA will develop uveitis in the 7 years following the onset of arthritis [4,5]. In 30% to 50% of children with JIA-associated uveitis, structural complications are present at the time of diagnosis [6]. Furthermore, about 50% to 75% of those with severe uveitis will eventually develop visual impairment secondary to ocular complications such as cataract, glaucoma, band keratopathy and macular pathology [7-9].

Defining the severity of inflammation and structural complications in uveitis patients can now be more consistently described by following Standardised Uveitis Nomenclature (SUN) guidelines and incorporating them into the design of randomised controlled trials (RCTs) and cohort studies [10]. Significant poor prognosticators of poor visual acuity include structural changes at presentation, the need for intraocular surgery, posterior segment inflammation, abnormal intraocular pressure and failure to maintain long-term disease control as marked by persistent anterior chamber (AC) cell scores of 1 or higher [6-8,11]. Despite current screening and therapeutic options (prebiologics), 10% to 15% of children with JIA-associated uveitis may eventually develop bilateral visual impairment and become certified legally blind [12,13]. It is therefore critical to find more effective therapeutic interventions for them.

### Rationale

Methotrexate (MTX) is well-established as the first-line disease-modifyin\g agent in the management of JIA [14,15]. The current approaches to the treatment of mild JIA-associated uveitis include use of topical steroids. MTX is also thought to be effective for JIA-associated uveitis in children with moderate to severe uveitis [16-18], but there have been no prospective, randomised, placebo-controlled trials of MTX or steroid regimens in JIA-associated uveitis. Systematic review of the evidence for the effectiveness of MTX in JIA patients is restricted to joint involvement [14], but not in paediatric uveitis. Despite the scarce evidence, MTX has become the mainstay of treatment for JIA-associated uveitis [19]. However, about 15% to 50% of affected children will have refractory uveitis in spite of optimal therapy with MTX [16-18]. De Boer *et al*. [13] found that uveitis was not controlled in 30% of patients started on MTX during the first year of therapy and that, even when remission was achieved with MTX, 9 of 13 later relapsed and only 4 (18%) of 22 patients achieved total remission. In the Great Ormond Street cohort, a similarly low proportion of 12% were found to be in total remission 5 years after initiation of MTX therapy [20]. Several agents, including ciclosporin and mycophenolate mofetil (MMF), have been shown to be of benefit in controlling JIA-associated uveitis in small retrospective case series [21,22]. However, their use remains restricted because of intolerability due to adverse reactions and little evidence that they rescue MTX-refractory patients. In addition, neither ciclosporin nor MMF is very effective in controlling joint manifestations in children [19]. More recently, animal models and corroborative human evidence [23] support the role of tumour necrosis factor α (TNF-α) in the aetiopathogenesis of uveitis and, moreover, the potential value of inhibiting TNF-α as a therapeutic intervention [24].

Studies utilising experimental models of autoimmune uveitis have demonstrated that TNF-α plays a pivotal role in the pathogenesis of intraocular inflammation [23], which has been borne out in the treatment of adult uveitis [24]. In mouse models of anterior uveitis, deleting the p55 receptor, as well as combined TNF receptor (TNFR) p55- and p75-knockout animals, resulted in reduced disease [25] more significantly than the effect of TNFR p55 fusion protein [26]. Furthermore, in an animal model of uveitis, infliximab reduced disease severity [27], albeit at doses of 20 mg/kg. Translating these data to humans, several case series have been published that have demonstrated the efficacy of anti-TNF-α therapies, including infliximab and adalimumab, in the treatment of severe refractory uveitis in adults and children [28-33]. In contrast, etanercept has been reported not to halt the onset of uveitis or to be more effective than placebo [34,35]. It also has been shown to be less effective than infliximab in treating JIA-associated uveitis [31,36,37]. A number of reports of new-onset uveitis associated with etanercept use in JIA have been published [38]. Investigators in an AE register–based study who examined these cases determined that whilst the frequency was greater for etanercept than for infliximab or adalimumab (*n* = 20; four and two cases, respectively), causality could not be established [39]. Etanercept is not considered to be effective in treating intraocular inflammation [31].

Adalimumab is a fully human monoclonal antibody engineered by gene technology that uses site-directed mutagenesis to enhance its binding efficiency to TNF-α. It does not contain nonhuman or artificial protein sequences. Adalimumab binds only to TNF-α and has a half-life of approximately 2 weeks. The antibody has been studied extensively *in vitro* and *in vivo* and has been shown not to be toxic in animal toxicology experiments. A clinical trial of adalimumab as monotherapy or in combination with MTX in adult patients with rheumatoid arthritis showed a significant clinical response [40]. A multicentre, randomised, double-blind, stratified parallel group trial showed a significant benefit in children with active JIA [41].

Retrospective case series in paediatric noninfectious uveitis treated with adalimumab have shown very promising results, with 21 of 26 eyes from among 14 children with JIA-associated or idiopathic uveitis showing improvement in inflammation [42]. In another retrospective case series of 18 paediatric patients with uveitis, 88% had a substantial decrease in ocular inflammation, and adalimumab showed corticosteroid-sparing potential [28].

To the best of our knowledge, no prospective studies of the efficacy and safety of anti-TNF agents in JIA-associated uveitis have been conducted to date. In the RCT of adalimumab in JIA that demonstrated safety and efficacy, the most commonly reported AEs were infections and injection site reactions [41]. SAEs considered possibly related to the study drug by the investigators occurred in 14 patients. Seven of these AEs included one case of bronchopneumonia, herpes simplex infection, pharyngitis and pneumonia, and there were two cases of herpes zoster infection. In that trial, there were no deaths, malignant conditions, opportunistic infections, cases of tuberculosis (TB), demyelinating diseases or lupus-like reactions [41]. The fixed-dose model of 20 mg for children weighing <30 kg and 40 mg for children weighing ≥30 kg selected for our current SYCAMORE Trial is based on the data generated in the above Lovell *et al*. trial using the same dosing regimen [41].

### Potential risks and benefits

JIA-associated uveitis is a severe, potentially sight-threatening condition that is often inadequately treated using standard therapies. The advent of biologic therapies offers significant anticipated benefits. However, due care must be taken in determining the potential benefits of anti-TNF therapy, which is now being used off-label for this condition, against the potential associated risks. The safety (short- and long-term) of the new biologic therapies in children and young people is of major importance, particularly in our present study. The risk-to-benefit assessment of this intervention needs careful attention. Safety is therefore a key secondary outcome measure of the trial.

### Potential risks

The long-term follow-up of children on etanercept and adalimumab therapy described in the controlled studies published to date have not shown any increased risk of malignancies. However, the US Food and Drug Administration (FDA) recently issued an alert to healthcare professionals that its analysis has revealed that 48 children developed malignancies whilst on anti-TNF agents, and 11 of the children died [43]. The data are derived mainly from children and adolescents on etanercept and infliximab therapy; data on adalimumab are scarce because of limited follow-up. The analysis includes, in particular, children with Crohn’s disease. Of the 48 children, 88% were taking concomitant immunosuppressive medication, including azathioprine and MTX. The complete details of the FDA analysis are not currently available. Importantly, these data do not provide comparative information on long-term malignancy rates in JIA patients treated with MTX alone or in patients with untreated JIA. Subsequently, a presentation at the American College of Rheumatology (ACR)/Associate Rheumatology Health Professional 2009 Annual Scientific Meeting reported that in 1,168 patients over 16,396 patient-years, no increased risk of anti-TNF therapy in JIA patients was found [44]. Recent data presented at the European League Against Rheumatism emphasises the importance of comparing anti-TNF safety data to untreated disease [45] and that current data do not indicate a significant relative increase with respect to controls [46]. All these reports, however, emphasise the critical importance of making safety a major priority in this trial. This priority is both within the treatment and follow-up duration of the trial, but procedures are also in place to continue this safety follow-up for the longer term.

The risk of increased malignancy with azathioprine in patients with Crohn’s disease on infliximab is well-recognised [47,48]. As noted already, AEs associated with the recent adalimumab trial in JIA were associated with minimal safety signals [41]. A recent retrospective cohort study evaluated overall mortality and cancer mortality in relation to immunosuppressive drug exposure, including anti-TNF drugs, in adult patients with ocular inflammatory diseases [49]. The study did show an increased overall and cancer mortality in adult patients exposed to anti-TNF agents. The study’s authors acknowledge that these data need to be interpreted with caution because of the methodological issues associated with retrospective studies and the prevalence of comorbidity in patients taking anti-TNF drugs.

On the basis of adult patient data, as well as on the growing evidence base of published data derived from long-term follow-up in biologic registries, clinical trials and cohort studies, a number of important safety signals need to be considered in this trial. Patients taking TNF blockers are more susceptible to serious infections. Patients must therefore be monitored closely for infections, including TB, before, during and after treatment with adalimumab. Because the elimination of adalimumab may take up to 5 months, monitoring should be continued throughout this period.

AEs of the haematologic system, including medically significant cytopaenia (for example, thrombocytopaenia, leucopaenia) have been reported with adalimumab. All patients should be advised to seek immediate medical attention if they develop signs and symptoms suggestive of blood dyscrasias (for example, persistent fever, bruising, bleeding, pallor) while on adalimumab.

Adalimumab monotherapy, as well as concomitantly with MTX, has been studied in rheumatoid arthritis, polyarticular JIA and psoriatic arthritis patients [41]. Antibody formation to adalimumab itself was lower when adalimumab was given together with MTX compared to adalimumab monotherapy. Administration of adalimumab without MTX resulted in increased formation of antibodies, increased clearance and reduced efficacy of adalimumab. In patients with polyarticular JIA, adalimumab antibodies were identified in 27 (15.8%) of 171 patients treated with adalimumab. In patients not given concomitant MTX, the incidence of adalimumab antibodies was 22 (25.6%) of 86, compared to 5 (5.9%) of 85 when adalimumab was used as an add-on to MTX.

Patients who develop a new infection while undergoing treatment with adalimumab should be monitored closely and should undergo a complete diagnostic evaluation. Administration of adalimumab should be discontinued if a patient develops a new serious infection or sepsis, and appropriate antimicrobial or antifungal therapy should be initiated until the infection is controlled. Physicians should exercise caution when considering the use of adalimumab in patients with a history of recurring infection or with underlying conditions which may predispose them to infections, including the use of concomitant immunosuppressive medications. Serious infections seen in clinical trials include pneumonia, pyelonephritis, septic arthritis and septicaemia.

### Known potential benefits

In rheumatoid arthritis phases I to IV studies [50], all individual components of the adult ACR response criteria (number of tender and swollen joints, physician and patient assessment of disease activity and pain, disability index Health Assessment Questionnaire scores and C-reactive protein (mg/dl) levels) improved at 24 or 26 weeks compared to placebo. In these studies, adalimumab-treated patients achieved statistically significant improvement in their rheumatoid arthritis symptoms based on ACR criteria showing 20% improvement (ACR20) and ACR50 responses compared to placebo as early as 1 to 2 weeks after initiation of treatment.

In polyarticular course JIA, adalimumab has been shown to have a significant clinical benefit in improving JIA on the basis of core paediatric ACR response criteria [51]. In the double-blind withdrawal design phase of the trial of adalimumab in JIA patients [41], amongst patients not receiving MTX, there was a significant increase in the number of disease flares in those patients who subsequently received placebo compared to those given adalimumab (71% vs. 43%; *P* = 0.03) [52]. In those patients receiving concomitant MTX, flares occurred in 65% on placebo compared to 37% who received adalimumab (*P* = 0.02). At 48 weeks, the percentage of patients treated with MTX who had ACR Pediatric 30 response criteria (Pedi 30), Pedi 50, Pedi 70 and Pedi 90 responses was significantly greater for those treated with adalimumab than for those given placebo (ACR Pedi 30: 63% vs. 38%, *P* = 0.03; ACR Pedi 50: 63% vs. 38%, *P* = 0.03; ACR Pedi 70: 63% vs. 27%, *P* = 0.002). Open-label extension of the studies showed sustained responses for up to 104 weeks of treatment. As outlined in the protocol rationale, its reported use in JIA-associated uveitis warrants a RCT trial to assess its clinical effectiveness and safety.

## Methods/design

### Trial design

The SYCAMORE Trial will randomise 154 patients ages 2 to 18 years with active JIA-associated uveitis (despite MTX treatment for at least 12 weeks). All participants will be treated for 18 months, with follow-up of 3 years from randomisation (continuing on MTX throughout). All participants will receive a stable dose of MTX as well as either adalimumab (20 mg/0.8 ml for patients <30 kg or 40 mg/0.8 ml for patients weighing 30 kg or more, subcutaneous injection every 2 weeks based on body weight) or placebo (0.8 ml as appropriate according to body weight) by subcutaneous injection every 2 weeks. Figure 1 shows the schematic of trial design.

**Figure 1 F1:**
[figure not shown]
**Schematic of trial design and patient journey.** AE, adverse event; CRF, case report form; MTX, methotrexate; OPD, Outpatient Department; QoL, quality of life.

### Regulatory approval

Full ethical approval was granted by the London Hampstead Research Ethics Committee (11/LO/0425). Full approval also was given by the Medicines and Healthcare Products Regulatory Agency (EudraCT 2010-021141-41).

### Primary end point

The primary end point of the study is ‘time to treatment failure’. *Treatment failure* is defined by one or more of the following factors:

1. Anterior segment inflammatory score grade (SUN criteria)

a. Two-step increase from baseline in SUN cell activity score (AC cells) over two consecutive readings

b. Sustained nonimprovement with entry grade of 3 or greater for 2 consecutive readings

c. Only partial improvement (+1 grade) or no improvement from baseline with development of other ocular comorbidities (defined below) that are sustained

d. Worsening of existing (upon enrolment) ocular comorbidities (defined below) after 3 months

e. Sustained scores recorded at entry grade measured over two consecutive readings (grade 1 or 2) still present after 6 months of therapy

In addition, following at least 3 months of therapy, treatment failure is met if any of the following factors are met:

2. Use of concomitant medications: at any time, requirement for concomitant medications in a manner outside predefined acceptable criteria or for any of the concomitant medications not allowed

3. Intermittent or continuous suspension of study treatment (adalimumab or placebo) for a cumulative period longer than 4 weeks

Ocular comorbidities are defined as follows: (1) disc swelling and/or cystoid macular oedema as gauged clinically and, where possible, by optical coherence tomography (OCT); and/or (2) raised intraocular pressure (>25 mmHg) sustained over two consecutive visits without any response to a single ocular hypotensive agent; and/or (3) hypotony (<6 mmHg) sustained over two consecutive visits; and/or (4) development of unexplained reduction in vision of 15 letters according to the logarithm of the minimal angle resolution (logMAR) over two consecutive visits (if the patient has cataracts, they will remain in the trial, even if cataract surgery is required; failure will remain as described in the end points described above).

Where a reading is must be sustained over two consecutive visits to define treatment failure, the time of treatment failure will be taken as the second of these readings.

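### By AC-cell score alone, a sustained one-grade worsening from entry grade 1 or 2 meets no failure criterion, while an unchanged score does

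*Protocol article*

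**What the plan says.** The Primary end point section of the protocol article defines treatment failure as one or more of a list of criteria. Three of them turn on the AC-cell grade alone:

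- 1a: "Two-step increase from baseline in SUN cell activity score (AC cells) over two consecutive readings"
- 1b: "Sustained nonimprovement with entry grade of 3 or greater for 2 consecutive readings"
- 1e: "Sustained scores recorded at entry grade measured over two consecutive readings (grade 1 or 2) still present after 6 months of therapy"

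The other routes need something besides the cell grade:

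- 1c: "Only partial improvement (+1 grade) or no improvement from baseline with development of other ocular comorbidities (defined below) that are sustained"
- 1d: "Worsening of existing (upon enrolment) ocular comorbidities (defined below) after 3 months"
- 2: "requirement for concomitant medications in a manner outside predefined acceptable criteria or for any of the concomitant medications not allowed"
- Criterion 3 is met when trial medication has been interrupted, in one spell or several, for more than 4 weeks in total.

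The Inclusion criteria admit participants with sustained AC-cell activity of grade 1+ or more, so entry grades 1 and 2 are part of the intended population.

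**The concern.** A failure rule based on a severity grade should be monotone: if a given course counts as failure, a worse course from the same starting point should count too. Here 1b is written in terms of nonimprovement, which covers the same grade and anything worse. Criterion 1e, its counterpart for the lower entry grades, is written in terms of scores at the entry grade. Taken literally, a participant who enters at grade 1 and stays at grade 1 fails after 6 months, while one who enters at grade 1 and stays at grade 2 does not.

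The timing can also be perverse. If the worsened eye later returns to its entry grade for two consecutive readings after 6 months, 1e is met then, and the event is dated to a period when the eye was improving.

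This is the primary end point, analysed as time to failure. The first secondary end point, the number of participants failing treatment, inherits the same classification.

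**Working it through.** **Step 1. Apply the cell-grade criteria to every sustained course.** Take a sustained grade over two consecutive readings, after 6 months of therapy, with no comorbidity, no medication breach and no suspension. One step is taken as one whole grade. The rules are: 1a if the sustained grade minus the entry grade is at least 2; 1b if the entry grade is at least 3 and the sustained grade is at or above it; 1e if the entry grade is 1 or 2 and the sustained grade equals it.

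| Entry grade | Sustained 0 | 1 | 2 | 3 | 4 |
|---|---|---|---|---|---|
| 1 | – | fails (1e) | **no failure** | fails (1a) | fails (1a) |
| 2 | – | – | fails (1e) | **no failure** | fails (1a) |
| 3 | – | – | – | fails (1b) | fails (1b) |
| 4 | – | – | – | – | fails (1b) |

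The dashes are improvements. The two bold cells, 1 to 2 and 2 to 3, are the only worsenings that are not failures. If 1e is read as at or above the entry grade, exactly these two cells change and no others.

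**Step 2. Reproduce the plan's sample size.** The Sample size section gives failure of 60% versus 30%, 90% power, 5% significance and 2:1 allocation. The test's sidedness is not stated; two-sided is assumed. The two-proportion formula with continuity correction gives 47 placebo and 93 adalimumab, 140 in all, as stated. Without the correction it gives 42 and 83. The sample size is therefore not in question here.

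**Step 3. Illustrate the effect on power.** The article does not say how often the pattern occurs, so the recorded rates below are assumptions. With d = p1 − p2, pooled p = (47·p1 + 93·p2)/140, and c = ½(1/47 + 1/93) = 0.0160:

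power = Φ[(d − c − 1.96·se0)/se1], where se0 = √[p(1 − p)(1/47 + 1/93)] and se1 = √[p1(1 − p1)/47 + p2(1 − p2)/93].

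For 60% versus 30%: p = 0.4007, se0 = 0.0877, se1 = 0.0858, and (0.300 − 0.016 − 1.96 × 0.0877)/0.0858 = 1.31, so power is 90.4%.

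| Uncounted failures, placebo / adalimumab (percentage points, assumed) | Recorded rates | Power |
|---|---|---|
| 0 / 0 | 60% vs 30% | 90% |
| 2 / 1 | 58% vs 29% | 88% |
| 5 / 2.5 | 55% vs 27.5% | 85% |
| 5 / 2 | 55% vs 28% | 84% |
| 10 / 5 | 50% vs 25% | 79% |
| 10 / 3 | 50% vs 27% | 71% |

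The 2/1, 5/2.5 and 10/5 rows remove failures in proportion to the planned rates, so the planned 50% relative reduction is preserved. The other two loss rows remove relatively more from placebo.

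**The case against.** Four points can be made on the other side.

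**Other routes to failure.** A reader might infer from the gap that such an eye can never be a failure. The article does not support that. A worsened eye has not improved, so it fails under 1c if a sustained comorbidity develops, and it can fail under 1d, 2 or 3. Criterion 2 is also broader than starting a prohibited drug, since it covers use of medication outside predefined limits. Those limits are not in this condensed article, so how much of the gap criterion 2 closes cannot be judged. This stands, and it narrows the point to the AC-cell score alone. It does not close the gap, because each of these routes needs a separate event.

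**Intended meaning.** Criterion 1e may be meant as the slower counterpart of 1b, that is, no improvement from grade 1 or 2 by 6 months. That is plausible, but the text does not say it, and 1b shows that nonimprovement wording was available. Anyone applying 1e literally would misclassify.

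**Size and direction.** A reader might infer a definite loss of power, or a bias towards no effect. Neither is shown. The frequency is unknown, and so is any imbalance between arms. Some of these events would be delayed, not lost, because a further step up meets 1a and a return to entry grade meets 1e. The planned 60% also does not come from criteria 1a to 1e. It rests on cohort patients who had not achieved disease control (28 of 51, 55%), so subtracting from it mixes two definitions. All of this stands; the power figures are illustrations only.

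**Cost.** The trial has ethics and regulatory approval and had recruited 58 patients at manuscript submission, so this is an amendment to the primary end point and not merely an edit to a program. This too stands, but the change adds no assessment.

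**Conclusion.** The point holds in a limited form. On AC-cell grade alone, the rule is non-monotone for entry grades 1 and 2: unchanged fails, one step worse does not, two steps worse does. From entry grade 3, one step worse fails. The defect covers two transitions, 1 to 2 and 2 to 3, and follows from the text without any assumption about frequency.

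Its consequence for the trial cannot be sized from the article. On assumed recorded rates, continuity-corrected power falls from 90% to 84–85% (55% versus 27.5–28%) or to 71–79% (50% versus 25–27%); if the pattern is rare, the loss is small. That sustained one-step worsening is commoner on placebo, and so dilutes the comparison, is a reasonable expectation and not a documented fact.

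**What to change.** Reconcile 1e with the nonimprovement wording of 1b. For entry grade 1 or 2, define failure as sustained scores at or above the entry grade over two consecutive readings, still present after 6 months of therapy. Derive the event by program from the recorded AC-cell grades, in the same way for every participant, including the 58 already recruited. Settle the wording before any comparison by arm.

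The cost is a protocol amendment to the primary end point wording, with the approvals that this needs, and a matching change to the derivation. No new data are required: Table 1 already schedules slit-lamp biomicroscopy at screening and at every visit from month 1. The sample size need not be revised on this account.
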